### Population

To be eligible, patients should have been diagnosed with advanced cancer (with any cancer site) and treated or not with palliative intent (chemotherapy, analgesic radiotherapy, surgery without curative intent), with an ECOG or a WHO performance status ≥ 2, a life expectancy ≥ 1 month, and an age ≥ 18 years.

Patients should have been informed about the palliative stage of the disease and should have been followed for at least 1 month by a palliative caregiver to be included in the study.

The non-eligibility criteria are: a psychiatric disease that compromises understanding of the study objectives and/or informed consent and/or the inability of patients to follow the study design for psychological, social, family, or geographical reasons.

Written informed consent is required before inclusion.

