**Collected data and order of administration for QoL questionnaires**				

	**Arms**	**Arms**	**Arms**	**Arms**

Consent	A/B/C/D			

Questionnaires: QLQ-C15, MVQOLI and QUAL-E	A/B/C/D	A/B/C/D	B and D	

Questionnaires: MVQOLI, QLQ-C15 and QUAL-E			A and C	

Questionnaires: MVQOLI, QLQ-C15				D and C

Performance Status, Performance Palliative Scale	A/B/C/D	A/B/C/D	A, B, C, D	

Vital signs, pain (EVA)	A/B/C/D	A/B/C/D	A, B, C, D	

Care (Oncology, Psychology, and so on)	A/B/C/D	A/B/C/D	A, B, C, D	

Responsiveness question	A/B/C/D	A/B/C/D		D and C

^a^D1: First day, the day where the first QoL questionnaires will be completed; D3: 3 days after the first day administration

^b^Can be done D1 at the end of the day if the first was done early in the day

^c^Only MVQOLI and QUAL-E

The above randomization was chosen to explore methodological aspects to optimize QOL tools in the end-of-life setting.

It will allow us to assess the occurrence of an order effect on QoL level by investigating a halo effect and/or a framing effect. Since every patient should complete three questionnaires (MVQOLI, QUAL-E, and the QLQ-C15 PAL), completion of the first questionnaire could influence responses for the following questionnaires, resulting in different QoL levels. Moreover, this effect could be differential depending on the completion order. Since QUAL-E needs a face to face interview, it will be completed by the patient at the end for each arm.

The second randomization will investigate the added value of spontaneous QoL completion to capture clinically important changes in QoL that could have occurred between two planned QoL assessments.

For each allocated group a specific case report form (CRF) will be produced with the corresponding order of QoL questionnaires to prevent changes in completion order (that is, 'cross-over') after the randomization.

Furthermore, the date and time of completion for each QoL questionnaire will be collected. This will allow us to check the order of completion used by the patients.

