### Longitudinal analyses

QoL will be described at each follow-up and then longitudinally analyzed using a mixed model analysis of variance for repeated measurements to investigate and test a time trend for QoL [39-41]:

These models will have to take into account non-random missing data.

With simple imputation methods for sensitivity analyses:

Mean QoL score imputation: Means will be calculated for the whole population and for specific patient profiles (cancer location, age, sex, and so on) at each follow-up and then will be imputed for patients with missing QoL scores

Extreme QoL score imputation. This method could be used when the missing data are due to a pejorative event such as death or disease progression.

With 'pattern mixture' models [42,43]:

Qualitative variables will be created to describe missing QoL score profiles and to define patterns for these analyses (no missing score, intermittent and drop-out profiles).

Time until definitive QoL score deterioration:

Analyses of time until a definitive QoL score deterioration (TUDD) will be estimated using the Kaplan-Meier method [44].

The TUDD of a score will be defined as the time interval between randomization and the first decrease in the MCID score ≥ 5 points compared to the QoL score at inclusion with no further improvement in QoL score ≥ 5 points or in the case of patient who dropped out after a ≥ 5-point decrease, resulting in missing data.

Patients will be censored at the last QoL follow-up when no ≥ 5-point deterioration in the QoL score from baseline will be observed or for patients with a ≥ 5-point deterioration, but with a subsequent ≥ 5-point improvement as compared to baseline QoL score.

Patients with no available QoL scores will be included in the TUDD analysis, but censored immediately.

2. To assess the impact of therapeutic strategies on QoL at the end of life Since treatments and care strategies will be longitudinally collected, for exploratory purposes only, we will compare longitudinal QoL according to these strategies using mixed model analysis of variance and Log Rank tests and Cox models for the time to definitive QoL deterioration analyses.

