QoL will be described at each follow-up and compared at the inclusion (using Wilcoxon rank test) and then longitudinally analyzed using mixed model analyses of variance for repeated measurement [39-41] to test for the following: a therapeutic strategy effect whatever the follow-up; time effect whatever the therapeutic strategy; interactions between therapeutic strategy and follow-up; and effects of other clinical factors. The best model will be chosen according to the smaller Akaike's information criterion (AIC).

As for the TUDD approach, it will be compared with Log-Rank tests. Univariate and multivariate Cox analyses will be done to compute hazard ratios with 95% CI.

3. To assess the added value of spontaneous QoL completion to detect a clinically significant change in this setting

The proportion of patients who report at least one MCID during follow-up using the Jaeschke transition question will be compared according to the group allocated by randomization using univariate and multivariate logistic regressions.

We will also compute effect size (ES) and standardized response mean (SRM) to explore sensitivity to change according to spontaneous completion of a QoL questionnaire or not. We aim to demonstrate that with spontaneous completion of QoL questionnaires, ES and SRM will be improved.

For the sensitivity analysis, time to definitive QoL deterioration will also be estimated including this spontaneous completion of QoL questionnaires.

Analyses will be performed on an intent-to-treat principle.

4. To assess the effect of questionnaire order on QoL levels Longitudinal QoL analyses will be done as described above QoL will be described at each follow-up and compared at inclusion and then longitudinally analyzed using the mixed model analysis of variance for repeated measurements [39-41]. For the TUDD approach, it will be compared with Log-Rank tests. Univariate and multivariate Cox analyses will be done to compute hazard ratios with 95% CI.

Analyses will be performed on an intent-to-treat principle.

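### Secondary objective 2 compares time to QoL deterioration from randomization between strategies recorded during follow-up, with no rule to prevent immortal-time bias

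*Protocol article*

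**What the plan says.** Assessing the impact of therapeutic strategies on QoL at the end of life is one of the secondary objectives listed under Objectives. Its analysis is item 2 under Longitudinal analyses in the protocol article.

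- **Exposure.** "Since treatments and care strategies will be longitudinally collected, for exploratory purposes only, we will compare longitudinal QoL according to these strategies".
- **Tests.** A mixed model, and "Log Rank tests and Cox models for the time to definitive QoL deterioration analyses". The text that follows repeats this: "As for the TUDD approach, it will be compared with Log-Rank tests", with univariate and multivariate Cox models giving hazard ratios and 95% confidence intervals.
- **Clock.** "The TUDD of a score will be defined as the time interval between randomization and the first decrease in the MCID score" of at least 5 points, without later recovery.
- **Status.** The comparison is labelled exploratory: "for exploratory purposes only, we will compare longitudinal QoL according to these strategies using mixed model analysis of variance and Log Rank tests".
- **What is known at entry.** Table 1 has a row "Care (Oncology, Psychology, and so on" marked for all four arms at D1, at the retest and at each follow-up visit. Under Population, patients may enter "treated or not with palliative intent (chemotherapy, analgesic radiotherapy, surgery without curative intent". Item 2 also compares QoL at inclusion with a Wilcoxon test.

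The article does not say how, or at what moment, a patient is assigned to a strategy group. A statistical analysis plan is to be written before database lock.

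**The concern.** An ordinary log-rank test needs groups that are fixed when the clock starts. The stated reason for this comparison is that care is recorded during follow-up, so a strategy may begin after time zero. If a patient is placed from randomization in the group of a strategy started in month 3, the first three months count as time under that strategy. If the grouping looks only at what was started before deterioration, those months are also event-free by construction. The strategy then appears to delay deterioration even if it does nothing.

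The article uses nearly the same log-rank and Cox wording for questionnaire order (item 4). There it is sound, because order is randomized and fixed at time zero. Strategy is neither. At stake are hazard ratios with 95% confidence intervals that could be read as evidence that a palliative treatment protects QoL.

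**Working it through.** The article gives no event rate, hazard ratio or power for objective 2, so there is no stated figure to reproduce. Every rate below is an assumption.

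**Hand check of the mechanism.** Assume exponential times with medians of 2 months to deterioration, 4 months to death (which censors TUDD) and 2 months to strategy start, all independent and with no effect.

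- Monthly rates (ln 2 / median): deterioration 0.347, death 0.173, start 0.347; sum 0.866.
- Share starting before deterioration or death: 0.347 / 0.866 = 0.40.
- Mean TUDD follow-up, non-starters: 1 / 0.866 = 1.154 months.
- Mean TUDD follow-up, starters: 1.154 waiting + 1 / (0.347 + 0.173) = 1.154 + 1.924 = 3.078 months.
- Share of follow-up ending in deterioration, both groups: 0.347 / 0.520 = 0.667.
- Crude rates with fixed groups from randomization: 0.667 / 3.078 = 0.217 against 0.667 / 1.154 = 0.578. Ratio 0.375, although the true ratio is 1.
- Waiting time moved to the unexposed side, per patient in the cohort:
  - exposed: (0.40 × 0.667) / (0.40 × 1.924) = 0.347
  - unexposed: (0.60 × 0.667) / (0.60 × 1.154 + 0.40 × 1.154) = 0.347
  - ratio 1.0

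**Simulation.** True hazard ratio 1, n = 372 (the planned inclusion), 200 replicates per scenario, Cox Wald test at two-sided 5%. Times are exponential; the last row adds a shared gamma frailty (variance 0.5) linking deterioration and death. Each cell gives hazard ratio / rejection rate.

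| Median months: deterioration, death, start | Started before deterioration or censoring, fixed group | Ever started before death, fixed group | Group set at baseline | Time-dependent covariate |
|---|---|---|---|---|
| 2, 4, 1 | 0.23 / 100% | 0.99 / 7% | 0.99 / 7% | 1.00 / 7.5% |
| 2, 4, 2 | 0.32 / 100% | 1.01 / 4.5% | 1.01 / 4% | 1.00 / 4% |
| 2, 4, 4 | 0.38 / 100% | 0.98 / 6% | 1.01 / 4.5% | 0.97 / 3% |
| 1, 2, 1 | 0.33 / 100% | 1.00 / 3.5% | 1.01 / 4.5% | 1.02 / 5.5% |
| 3, 6, 2 | 0.28 / 100% | 1.00 / 5% | 1.00 / 7.5% | 0.99 / 5.5% |
| 2, 4, 2, frailty | 0.21 / 100% | 0.69 / 58% | 0.99 / 3.5% | 0.99 / 5% |

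The second row is the hand-check scenario. Cox gives 0.32 rather than 0.375 because hazards are no longer constant once patients are grouped this way. With 200 replicates, the Monte Carlo range around 5% is 0.05 ± 1.96 × √(0.05 × 0.95 / 200), or 2.0% to 8.0%. Baseline groups and time-dependent coding stay within it throughout.

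**Why the second grouping behaves differently.** Deterioration is not terminal, and questionnaires continue monthly until death. A strategy can therefore start after deterioration, and having ever received it does not by itself guarantee event-free time. It does select longer survivors, which matters once survival and deterioration are linked. Item 5 expects such a link for some dimensions: those tied to health status should fall near the end of life.

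**The case against.** The strongest reply is that the article states no grouping rule, so the error is supposed rather than planned. Care is recorded at D1 and at retest, both before randomization. Patients enter on or off treatment, and QoL is compared at inclusion, which fits groups that already exist then. Cox models can take time-dependent covariates, nothing excludes them, and exposure coding is commonly left to the analysis plan. The analysis is exploratory and touches neither the reproducibility outcome nor the randomized comparisons.

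Much of this stands. A reader might infer that the bias is built in, or that any strategy started after randomization will look protective. The documents support neither: baseline groups remain possible, and the ever-started grouping is unbiased when deterioration and death are independent. A reader might also take the survival comparison to be the only analysis of this objective. It is not; mixed models are planned too, and they have no event-free waiting time of this kind.

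It does not remove the point. This is more than a missing detail, because the article fixes the source of the exposure, the time origin and the test, and the three do not fit together for a strategy that starts later. A comparison at inclusion does not show that groups are defined at inclusion. The exploratory label limits the weight of the result but does not correct a systematic bias.

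**Conclusion.** The concern holds conditionally. As worded, the TUDD comparison by strategy is open to immortal-time bias, because no rule says whether strategy is fixed at inclusion or follows its start date. If strategies started after randomization are used as fixed groups, the size depends on the rule:

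- started before deterioration or censoring: hazard ratio about 0.2 to 0.4, 100% false rejection;
- ever started before death: about 0.7 with 58% false rejection under the one correlation assumed, and about 1.0 under independence;
- defined at baseline: no such bias.

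These figures rest on assumed medians (deterioration 1 to 3 months, death 2 to 6, strategy start 1 to 4), exponential times and one frailty variance. They show direction and order of magnitude and are not a forecast for this cohort. Severity is low to moderate: a stated secondary objective is affected, but an exploratory one.

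**What to change.** State the exposure rule for objective 2 in the analysis plan:

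1. For log-rank tests, define strategy groups only by the care in place at inclusion, which Table 1 already records at D1.
2. In the Cox TUDD models, enter strategies started later as time-dependent covariates, with the patient counted as exposed only from the start date.
3. Do not use the log-rank test for strategies started after randomization.

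Leave the mixed models as they are on this ground.

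The cost is a few sentences and start-stop coding of care data the study already plans to record, so slightly more programming. If only visit-level records exist, exposure can begin at the visit where the strategy first appears; the article does not say whether exact start dates are kept. Under Trial status, 12 of 372 patients had been included, so the change comes early. It does not remove confounding by indication, so the analysis should remain exploratory.

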### Completion of QoL questionnaire

The QoL questionnaires will be completed before randomization and then every month until death in a time driven design fashion.

Using test-retest methodology, the QLQ-C15 PAL, MVQOLI, and QUAL-E questionnaires will be completed 3 days after the first completion at baseline and before randomization [27].

Though a maximum delay of 15 days is usually allowed between completions to check reproducibility, since these patients have a specific end-of-life profile with sometimes a rapid deterioration in general health status, a maximum delay of 3 days was chosen to minimize the 'risk' of changes in health status.

Since the QUAL-E questionnaire should be completed using a direct interview; patients should complete it last to prevent social desirability bias on QLQ-C15 PAL and MVQOLI evaluations [27].

In order to prevent missing QoL data [28], if a patient is unable to complete questionnaires due to poor health status, QLQ-C15 PAL and MVQOLI could be completed with the help of a proxy (from the medical team) who will have to record the patient's answers without interpretation [29]. A specific item will be completed to take this information into account for the longitudinal analysis of QoL.

All patients will complete QoL questionnaires every month until death.

In arms C and D, depending on patients' health status or perceived QoL, patients will be free to complete the QLQ-C15 PAL and MVQOLI questionnaires (spontaneous QoL completion in an event drive design) between two planned evaluations. A patient CRF including QLQ-C15 PAL and MVQOLI questionnaires, the date of completion, the perception of QoL changes using the Jaescke transition question [30]), and a space for free comments will be created. This booklet will be given to the patients after randomization.

The QoL questionnaires will be administered in a homogeneous way by the same person, a nurse specialized in palliative care, a psychologist, or if necessary a clinical research assistant (CRA), throughout the patient follow-up until death.

Completed questionnaires should be returned to one of the CRAs assigned to the study. In order to deal with holidays, a minimum of two full-time CRAs will be required and identified for each participating center (Table 2).

**Table 2 T2:** Center's participation agreement

Organization	City
Cancer care center Paul Papin	Angers, France

Cancer care center Léon Bérard	Lyon, France

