### Statistical analyses

A statistical analysis plan will be written before the database is locked.

The population and clinical characteristics will be described (sex, age, family situation, cancer site).

The rate of QoL completion will be described for each questionnaire at each follow-up. QoL scores will be described at each follow-up.

Continuous variables will be described by means (standard deviation) and median (minimum-maximum). Qualitative variables will be described by frequencies and percentages.

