#### Secondary objectives

1. To longitudinally assess QoL of cancer patients until death using QLQ-C15 PAL, the French version of QUAL-E, and of Missoula Vitas Quality of Life Index (MVQOLI) Statistical analyses will be conducted to investigate longitudinal changes of each QoL dimension: description of missing QoL scores; missing QoL questionnaires and scores will be studied and classified according to Diggle and Rubins' method to determine whether the missing data were random or not: Missing Completely At Random, Missing At Random, Missing Not At Random [30,31,37,38].

Univariate and multivariate Logistic regression will be done to construct a clinical model to predict missing QoL and to investigate the random nature of missing QoL data. The numbers of missing scores will be described according to the patient subgroups and compared using ANOVA and Mixed Anova for repeated measurement.

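### Questionnaire order is tested on QoL levels without comparing completion by order, so sicker patients leaving the second form blank could produce a false order effect

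*Protocol article*

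**What the plan says.** Under Randomization and Table 1, MVQOLI is given first in arms A and C and second in B and D at every monthly assessment until death; QLQ-C15 PAL takes the opposite place. QUAL-E is last in all four arms. The stated reason for randomizing order is a halo or framing effect, meaning that the first form may change the answers given on later ones.

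Objective 4 (under Longitudinal analyses) reads: "To assess the effect of questionnaire order on QoL levels Longitudinal QoL analyses will be done as described above". The methods are a repeated-measures mixed model and time until definitive deterioration, and "Analyses will be performed on an intent-to-treat principle".

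The section referred to says of the models: "These models will have to take into account non-random missing data". It names two routes. The first is mean or extreme score imputation ("With simple imputation methods for sensitivity analyses"). The second is pattern-mixture modelling: "Qualitative variables will be created to describe missing QoL score profiles and to define patterns for these analyses", with the patterns none, intermittent and drop-out.

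On completion, Statistical analyses says "The rate of QoL completion will be described for each questionnaire at each follow-up", and Secondary objectives, item 1, says "The numbers of missing scores will be described according to the patient subgroups" and plans a logistic model to predict missing QoL. The allocated order is not named in any of these.

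Blank forms are foreseen. Completion of QoL questionnaire allows a member of the medical team to record answers on QLQ-C15 PAL and MVQOLI "if a patient is unable to complete questionnaires due to poor health status", and reasons for non-completion are collected.

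**The concern.** Order can act in two ways. It can change the answers, which is what the trial wants to learn. It can also change which form gets answered at all, because a tiring patient is more likely to stop before the second form than before the first. The article considers only the first route.

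Patients enter with performance status 2 or worse and are followed until death. If the sickest leave the second form blank more often, MVQOLI levels in A+C come from nearly everyone, while those in B+D come from the fitter patients who got that far. The reverse holds for QLQ-C15 PAL. A difference in who answered would then be read as a halo or framing effect. Randomization protects the comparison of all randomized patients, but not that of the patients who happened to answer.

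**Working it through.** The article gives no sample size, effect size or completion rate for the order comparison, so there is no figure of its own to reproduce. Every completion rate below is an assumption.

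**1. One visit, no true order effect.** Inputs: 372 patients allocated 1:1:1:1, so 372/2 = 186 per order group; assumed SD 25 on a 0 to 100 scale; assumed correlation r between score and health of 0.5 to 0.8. A form is completed when health plus independent noise of equal variance exceeds a threshold t that gives completion rate c. Then:

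mean of completers above the true mean = SD × r × (1/√2) × φ(t)/c

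The values of φ(t)/c are 0.195 for c = 90%, 0.350 for 80%, 0.497 for 70% and 0.644 for 60%. For 90% against 80%: 25 × 0.707 × (0.350 − 0.195) = 2.74, times r = 1.37 to 2.2 points. The standard error is 25 × √(1/167.4 + 1/148.8) = 2.82.

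| Completed when first / second | False difference, points | In SD | Significant at nominal 5% |
|---|---|---|---|
| 90% / 90% | 0 | 0 | 5% |
| 90% / 80% | 1.4 to 2.2 | 0.05 to 0.09 | 8% to 12% |
| 90% / 70% | 2.7 to 4.3 | 0.11 to 0.17 | 15% to 31% |
| 80% / 60% | 2.6 to 4.1 | 0.10 to 0.17 | 13% to 26% |

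These are complete-case figures, not results of the planned models.

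**2. Pooled visit-mean imputation at one visit.** With equal groups, completion c1 and c2 and complete-case gap d, filling blanks with the pooled mean leaves d × 2·c1·c2/(c1 + c2). For 90% and 80% this is 1.44/1.70 = 0.85 of the gap. For 90% and 70% it is 1.26/1.60 = 0.79. Most of the bias stays.

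**3. Repeated visits with the named methods.** Simulation with no true order effect: 372 patients, up to 5 monthly visits, 15% monthly attrition. Health = patient effect (SD 0.75) − 0.15 per month + visit noise (SD 0.5); form error SD 0.45, so the score SD is √(0.5625 + 0.25 + 0.2025) ≈ 1. The second form is blank with logit a − 2 × health. There were 100 trials per setting and one reading of each named method. Cells give the false effect (share significant at 5%).

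| Second forms blank | Mixed model | Pattern mixture | Visit-mean imputation |
|---|---|---|---|
| 14% | 0.08 SD (24%) | 0.06 SD (16%) | 0.14 SD (57%) |
| 22% | 0.12 SD (42%) | 0.11 SD (37%) | 0.21 SD (91%) |
| 31% | 0.18 SD (68%) | 0.17 SD (62%) | 0.26 SD (99%) |

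A separate run of the same health model, adjusted for baseline score (60 to 80 trials per setting), gave mixed-model effects of 0.05 to 0.06 SD at 13% blank (10% to 11% significant), 0.12 SD at 21% (40% to 43%) and 0.17 SD at 30% (74%). A further run gave about 0.05 to 0.2 SD over 13% to 30%; there visit-mean imputation was no better than the mixed model and often worse, up to 0.29 SD.

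**4. Imputing from same-visit data.** The false effect was 0.00 SD at 13% blank and 0.03 SD at 21%, with 5% and 7% significant. At 30% blank, 0.03 to 0.09 SD remained.

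**5. What a completion comparison can detect.** 186 against 186, two-sided 5%, one visit, all alive: power is about 31% for 90% against 85%, 77% for 90% against 80%, and 97% for 90% against 75%.

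**The case against.** **Missing data are already covered.** A reader might infer that the order effect is judged on completed forms only, with missingness ignored. The documents do not support that: the reference back to the earlier methods imports the requirement to handle non-random missingness, two imputation routes and pattern-mixture models. A patient with an occasional blank MVQOLI falls in the intermittent pattern. What remains is that the pattern does not record that the form came second, and in the simulation pattern-mixture models removed little of the bias.

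**The rest is SAP detail.** The article says an analysis plan will be written before database lock, and that plan may name order in the missingness model or the completion tables. This is fair, and it keeps the point modest. But the article does not leave the methods open. It names them, and for this comparison they do not suffice.

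**Completion is not the objective.** True: the objective is order and QoL levels. Completion by order is needed here to interpret the level result.

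**The sizes are assumed.** This stands. The simulations use a steep dependence on health and a score-health correlation of √(0.8125/1.015) ≈ 0.9. The article itself expects psychological and spiritual dimensions to stay stable or improve slowly, so the bias there could be smaller. With 60 to 80 trials, the Monte Carlo error is about 3.5 points at 10% significant, so the rejection rates at the lowest blank rate are imprecise.

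**Safeguards exist.** Help with recording answers is allowed on exactly the two swapped forms, and the same person administers the questionnaires throughout. Both may lower the number of blanks.

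**Imputing one form from the other could erase a real halo effect.** This is correct for a pooled imputation model, because a halo effect changes the relation between the forms by order. The imputation must therefore be fitted within each order group. The simulations contained no true order effect and cannot show this; it rests on reasoning.

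**Conclusion.** The concern holds in a limited form. The plan addresses non-random missingness in general. It does not compare completion by allocated order, and none of its named methods is stated to use the order or the health information from the same visit. If sicker patients leave the second form blank more often, a false order effect of roughly 0.05 to 0.2 SD can appear for assumed blank rates of 13% to 30%, and visit-mean imputation can leave or enlarge it. With equal completion by order there is no such bias. The point concerns MVQOLI and QLQ-C15 PAL; QUAL-E has the same position in every arm.

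A reader might also infer that any order effect found will be spurious. The documents do not support that: they give no completion rates, and completion may turn out equal.

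**What to change.** In objective 4:

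1. Compare the proportion of due MVQOLI and QLQ-C15 PAL forms completed between A+C and B+D, for example with a repeated-measures logistic model, and report it beside the level comparison. Give the estimate with its confidence interval: power for a gap of 5 percentage points at one visit is only about 31%, so a non-significant result does not show equal completion.
2. Add a sensitivity analysis for levels. For patients alive at the visit, multiply impute a blank form from the other form, the PPS and the pain score recorded at that visit, then fit the planned mixed model. Fit the imputation model separately within each order group so that a true halo effect is preserved.
3. Do not rely on visit-mean imputation for this comparison.

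The sensitivity analysis is best read beside the main result. Making it a condition for declaring an order effect would cost power that has not been assessed.

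Cost: analysis wording and modest programming. Table 1 already schedules the data needed. The imputation assumes that blanks are explained by same-visit data, so some bias may remain at high blank rates.
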